## Discussion

We have outlined the rationale and design of a randomised controlled trial to investigate whether, amongst patients awaiting physiotherapy treatment for distal upper limb pain, advice to remain active results in a long-term reduction in arm pain and disability, compared with advice to rest. Further, the trial gives rise to a pragmatic opportunity to examine whether, among the same patient population, immediate (‘fast-track’) physiotherapy results in a long-term reduction in arm pain and disability, compared with physiotherapy delivered at the usual time – typically, after a waiting list period of 6–8 weeks.

Patients awaiting physiotherapy for distal arm pain are commonly advised to rest the affected limb and avoid strenuous activities to ‘prevent further injury’. However, there is currently no sound evidence to support this strategy. The current trial is novel, in that it tries to address this, although similar strategies have been applied in other areas and have led to enormous clinical benefit. In low back pain, for >20 yrs the benefits of remaining active – as opposed to bed-rest, widely advocated at the time – have been well known. The evidence supporting maintenance of activity among persons with low back pain is now well established. Indeed recent studies from Australia have demonstrated that widespread publicity campaigns, promoting this message, result in a reduction in the number of claims for back pain compensation, and medical payments for back pain in the general population [19]. However, despite the epidemiological evidence to suggest that many regional pain syndromes share common aetiological and prognostic factors [13], there has been little extrapolation of these principles to other pain conditions.

The results of this trial will have an immediate influence on the management of patients with distal arm pain. Also, depending on the results, it may inform future research studies to refine management. For example, we may find that there is a worthwhile benefit from remaining active and maintaining usual activities while awaiting physiotherapy treatment. If this is the case, this would provide strong evidence that the advice currently given to patients with distal arm pain should be changed. Alternatively, if there is no additional benefit from advice to remain active, this would support the current treatment strategies and current advice that is given. It would also provide the stimulus for examining in more detail the differences between low back pain and distal arm pain – i.e. why, when the risk factors for long-term pain and disability are similar, do similar treatment approaches fail to work?

In addition, we may find that ‘fast-track’ physiotherapy has beneficial outcomes, compared to physiotherapy delivered at the usual time. This would provide good evidence in support of a rapid-access policy which, in turn, would translate into clear and immediate patient benefit. It would be unethical to conduct a study where some patients received physiotherapy and others did not. However, if the current trial demonstrates that there is no additional benefit from early physiotherapy, this would provide the rationale (and the ethical justification) for randomised trials of specific physiotherapeutic modalities. This might lead to more refined physiotherapy treatments and more efficient use of healthcare resources.

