**Methods/Design:**

Between January 2012 and January 2014, new referrals to 14 out-patient physiotherapy departments were screened for potential eligibility. Eligible and consenting patients were randomly allocated to one of the following three groups in equal numbers: 1) advice to remain active, 2) advice to rest, 3) immediate physiotherapy. Patients were and followed up at 6, 13, and 26 weeks post-randomisation by self-complete postal questionnaire and, at six weeks, patients who had not received physiotherapy were offered it at this time. The primary outcome is the proportion of patients free of disability at 26 weeks, as determined by the modified DASH (Disabilities of the Arm, Shoulder and Hand) questionnaire.

We hypothesise (a) that advice to maintain usual activities while awaiting physiotherapy will be superior than advice to rest the arm; and (b) that fast-track physiotherapy will be superior to normal (waiting list) physiotherapy. These hypotheses will be examined using an intention-to-treat analysis.

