### Statistical issues

#### Proposed sample size/power calculation

The study is powered to determine a difference in the proportion of patients fully recovered at 26 weeks post-randomisation, as assessed using the modified DASH. The principal analysis will consist of a comparison between participants in Group 1 and Group 2 (advice to maintain usual activities, versus advice to rest the arm). We have previously shown that, among persons with distal arm pain undergoing usual care, 51% were free of disability at six months, with little further improvement (up to 60%) at 12 months [5]. The trial is powered on the assumption that 70% of participants in Group 1 will be free of disability at six months. We require 148 subjects in each group in order to detect this difference with 90% power and an alpha of 5%. From previous trials with similar follow-up methods we anticipate, conservatively, that 80% of patients randomised will complete a follow-up questionnaire at 26 weeks [18]. Thus, we need to randomise 185 participants per group. We intend, in addition, to recruit 185 participants into Group 3 (immediate physiotherapy). Thus, we aimed to randomise 555 participants in total.

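### The Discussion treats no additional benefit from active advice as support for current rest advice, an inference that a superiority trial with an 11-point confidence half-width does not carry

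*Protocol article*

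**What the plan says.** The abstract (Methods/Design) frames both questions as superiority: that "advice to maintain usual activities while awaiting physiotherapy will be superior than advice to rest the arm", and that "fast-track physiotherapy will be superior to normal (waiting list) physiotherapy".

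The section on proposed sample size sets the trial's size on Group 1 against Group 2 only. From an earlier study under usual care it takes that "51% were free of disability at six months". It then states: "The trial is powered on the assumption that 70% of participants in Group 1 will be free of disability at six months". It concludes: "We require 148 subjects in each group in order to detect this difference with 90% power and an alpha of 5" per cent. Group 3 is added at the same size, with no effect size or power for the physiotherapy comparison.

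The Statistical analysis section plans, for both comparisons, the absolute difference in the probability of full recovery with a 95% confidence interval. The article gives no equivalence margin and no smallest worthwhile difference.

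The Discussion then says what a null result would mean. For advice: "if there is no additional benefit from advice to remain active, this would support the current treatment strategies and current advice that is given". For physiotherapy: "if the current trial demonstrates that there is no additional benefit from early physiotherapy, this would provide the rationale (and the ethical justification") for trials of specific treatment modalities.

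**The concern.** A superiority trial that finds no significant difference has not shown that there is none. How much benefit it rules out depends on the width of the confidence interval, and the Discussion sentence on advice takes no account of that.

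There is a second gap, which does not depend on sample size. If the two kinds of advice gave exactly equal outcomes, that would be no argument for rest over activity. The article itself says, in the Background and again in the Discussion, that advice to rest has no sound evidence behind it. Equal outcomes would leave the choice open.

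At stake is the published conclusion. The Discussion expects the results to influence management at once. A non-significant result could be reported as backing existing advice while the data remain compatible with a sizeable benefit from staying active.

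**Working it through.** **Inputs from the article:** 51% and 70% recovered; 148 evaluable per group; two groups pooled against Group 3 for physiotherapy (148 against 296); and the expectation that "80% of patients randomised will complete a follow-up questionnaire at 26 weeks".

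**Assumptions:** unadjusted normal approximations; 51% recovery in the comparison group; margins of 5, 10, 15 and 19 points, shown as a range because the article gives none.

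**1. The article's own figure.** Two-sided test at 5%, 90% power, mean proportion 0.605:
- Without continuity correction: n = [1.96 × √(2 × 0.605 × 0.395) + 1.2816 × √(0.51 × 0.49 + 0.70 × 0.30)]² / 0.19² ≈ 137.03, rounded up to 138.
- With continuity correction: (137.03 / 4) × [1 + √(1 + 4 / (137.03 × 0.19))]² ≈ 147.4, rounded up to 148.
- 148 / 0.80 = 185 per group; 3 × 185 = 555.

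The sample size reproduces exactly and is not in question.

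**2. Precision for Group 1 against Group 2.** SE at 51% in both arms = √(2 × 0.51 × 0.49 / 148) = 0.0581. Half-width = 1.96 × 0.0581 = 0.114, about 11 points.

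**3. Chance of a non-significant result when there is a true benefit** (uncorrected test, 148 per arm, 51% in Group 2):

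| True benefit | Power | Non-significant |
|---|---|---|
| 5 points | 14% | 86% |
| 10 points | 41% | 59% |
| 15 points | 75% | 25% |
| 19 points | 92% | 8% |

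Power passes 50% at about 11 points.

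**4. A result just short of significance.** Observed 62% against 51%: SE = √[(0.62 × 0.38 + 0.51 × 0.49) / 148] = 0.0573. The interval is 0.11 ± 0.112, about -0.2 to +22 points. The upper limit lies above the 19 points for which the trial was sized.

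**5. If there is truly no difference, how often is a given benefit excluded?** P(upper limit < m) = Φ(m / 0.0581 − 1.96):

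| Assumed margin m | Chance that it is excluded |
|---|---|
| 5 points | 14% |
| 10 points | 41% |
| 15 points | 73% |
| 19 points | 90% |

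**6. Physiotherapy comparison.** Half-width = 1.96 × √[0.51 × 0.49 × (1/148 + 1/296)] = 0.099, about 10 points. Power is about 51% for a true 10 points and reaches 90% at about 16 points.

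**The case against.** The strongest reply is that the Discussion states no rule. The sentences are conditional and forward-looking, and neither mentions a p-value. The physiotherapy sentence even asks that absence of benefit be demonstrated, which is more than a failed superiority test. Support for current advice might be read loosely, as no reason to change it. Confidence intervals for the absolute difference are already planned, and an analysis plan that is not shown may hold rules for reading them.

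Much of this stands. The text is not a formal decision rule, and no primary test is invalid. The lack of a margin would not be a fault on its own. What remains is the inference that the article does print: no additional benefit, therefore support for current advice. The looser reading does not rescue it, because giving no reason to change advice is different from supporting it.

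A reader might also infer more than the documents support:
- *Any true effect below 19 points would most likely be missed.* It would not. Power passes 50% at about 11 points and is about 75% at 15.
- *The trial cannot show absence of any benefit.* It can exclude large ones. An observed difference of zero excludes benefits above about 11 points.
- *The 19-point sizing governs both comparisons.* It applies only to Group 1 against Group 2.
- *The article confuses the timing of physiotherapy with its efficacy.* The abstract, the aims and the Discussion define the second aim as immediate against waiting-list treatment, and the Discussion never says that a null result would show physiotherapy to be ineffective.

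**Conclusion.** The point holds as a fault in the stated interpretation, not in the design, the sample size or the primary analysis. With about 148 evaluable per arm, a non-significant comparison of the two kinds of advice could leave a benefit of up to about 22 points open. Whether a null result excludes a worthwhile benefit depends heavily on what counts as worthwhile: if there is no true difference, the chance runs from 14% for a 5-point margin to 90% for 19 points. Whatever the sample size, equal outcomes would not favour rest over activity.

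For early physiotherapy the issue is milder. The wording is more careful and the pooled comparison somewhat more precise, but no effect size or power is stated, so a null result needs the same reading from its interval.

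The figures assume 80% completion and 51% recovery in the comparison group. They ignore covariate adjustment and the bootstrap, so the intervals actually obtained may differ somewhat.

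**What to change.** - Remove the statement that a lack of additional benefit from active advice would support current strategies and advice.
- State that a non-significant result in either comparison will be read from the 95% confidence interval for the absolute difference, which is already planned.
- Fix a smallest worthwhile difference before the results are seen. Claim no worthwhile benefit, for either comparison, only if the upper limit lies below it; otherwise call the result inconclusive.
- Make the physiotherapy sentence depend on the same condition.

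The article says that follow-up was still under way, so this could be settled before the analysis. It needs no new patients, data or models: a few sentences and one agreed difference. The cost is that a null result will support a weaker claim than the article now promises, and by the figures above it may often have to be called inconclusive if the agreed difference is 10 points or less.

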### Ethics

South Central – Hampshire A Research Ethics Committee (reference number: 11/SC/0107).

## Abbreviations

DASH: Disabilities of the Arm, Shoulder and Hand; NHS: National Health Service; QALY: Quality Adjusted Life Year.
